## Abstract

**Background:**

Septic shock is a major public health problem that is associated with up to 50% mortality. Unfavorable outcomes are mainly attributed to multiple organ failure (MOF) resulting from an uncontrolled inflammatory response and ischemia-reperfusion processes. REmote ischemic COnditioning (RECO) is a promising intervention to prevent ischemia-reperfusion injury. We hypothesize that RECO would reduce the severity of septic shock-induced MOF.

**Methods/design:**

RECO in septic shock patients (RECO-Sepsis study) is an ongoing, prospective, multicenter, randomized, open-label trial, testing whether RECO, as an adjuvant therapy to conventional treatment in septic shock, decreases the severity of MOF as assessed by the Sequential Organ Failure Assessment (SOFA) score. Adult patients admitted to an intensive care unit with documented or suspected infection, lactatemia > 2 mmol/l, and treated with norepinephrine for less than 12 h are potentially eligible for the study. Non-inclusion criteria are: having expressed the wish not to be resuscitated, contraindication for the use of a brachial cuff on both arms, intercurrent disease with an expected life expectancy of less than 24 h, cardiac arrest, and pregnant or breastfeeding women. After enrollment, patients are randomized (*n* = 180) 1:1 to receive RECO or no adjunctive intervention. RECO consists of four cycles of cuff inflation to 200 mmHg for 5 min and then deflation to 0 mmHg for another 5 min. RECO is performed at inclusion and repeated 12 and 24 h later. The primary endpoint is the mean daily SOFA score up to day 4 after inclusion. Secondary outcomes include the need for organ support, hospital length of stay, and 90-day mortality.

**Discussion:**

Results of this proof-of-concept trial should provide information on the efficacy of RECO in patients with septic shock.

**Trial registration:**

ClinicalTrials.gov, ID: identifier: NCT03201575. Registered on 28 June 2017.

**Electronic supplementary material:**

The online version of this article (10.1186/s13063-019-3406-4) contains supplementary material, which is available to authorized users.

## Background

Septic shock is a major and growing public health problem affecting millions of patients worldwide annually and 10 to 30% of patients admitted to intensive care units (ICUs) [1]. Despite regularly updated international guidelines and significant improvement in the treatment of septic shock, short-term mortality, which is mostly attributed to multiple organ failure (MOF), still remains as high as 50% [1, 2]. In view of these alarming figures, there is a compelling need for new therapeutic approaches to prevent MOF and thereby improve survival in this disease.

The pathophysiology of septic shock-induced MOF is complex and remains incompletely understood. It is recognized that it results, at least in part, from an uncontrolled systemic inflammatory response and ischemia/reperfusion (I/R) processes related to transient arterial hypotension, low cardiac output, and compromised microcirculation with cellular hypoxia/reoxygenation and mitochondrial dysfunction [2–4]. However, among the first-line treatments recommended for patients with septic shock (i.e., antibiotics, source control of infection, fluids, and vasoactive drugs), none specifically targets I/R injury [2].

REmote ischemic COnditioning (RECO) represents an innovative strategy to protect organs (e.g., brain, heart, kidneys) against the deleterious effect of I/R through activation of cell survival pathways and modulation of the inflammatory response [5–8]. RECO usually consists of applying brief and repeated cycles of non-lethal ischemia alternating with reperfusion by inflating and deflating a blood pressure cuff placed around a limb [5–8]. Over the past few years, this simple, inexpensive, non-invasive, and innocuous intervention has been investigated in numerous clinical trials with promising results [9–13]. For instance, it has been shown that RECO may limit myocardial damage after both acute myocardial infarction [9] and on-pump cardiac surgery [10]. Beyond protection of the heart, RECO has also been reported to be nephroprotective and neuroprotective, suggesting a ubiquitous effect of this intervention in humans [11–13]. Specifically for septic shock, only pre-clinical data are available and these indicate clear benefits of RECO, including survival, in both small and large animals [14–16].

To the best of our knowledge, RECO has not been tested in patients with septic shock. We have, therefore, implemented a multicenter, randomized controlled trial (RECO-Sepsis study) to investigate whether ischemic conditioning applied by inflating/deflating a cuff around an upper limb would limit the severity of MOF in septic shock patients.

## Methods/design

### Design and setting

The trial protocol was developed in accordance with the SPIRIT (Standard Protocol Items: Recommendations for Interventional Trials) guidelines [17] (Additional file 1). RECO-Sepsis is a prospective, multicenter, randomized, open-label, parallel-group trial, testing whether RECO as an adjuvant therapy to conventional treatment in septic shock would decrease the severity of MOF as measured by the Sequential Organ Failure Assessment (SOFA) score [18–21]. The trial is conducted in French intensive care units (ICUs). An overview of enrollment, interventions, and follow-up of participants in the RECO-Sepsis trial is shown in Figs. 1 and 2. The trial is supported by a grant from the French Ministry of Health (Programme Hospitalier de Recherche Clinique Inter-régional 2016) and the study sponsor is the Hospices Civils de Lyon. The study was registered at ClinicalTrials.gov (NCT03201575) on 28 June 2017.

**Fig. 1 Fig1:**
[figure not shown]
Schedule of enrollment, interventions, and assessments according to Standard Protocol Items: Recommendations for Interventional Trials (SPIRIT). *ICU* intensive care unit

**Fig. 2 Fig2:**
[figure not shown]
Flow chart

### Ethics

The trial is conducted in accordance with the principles of the Declaration of Helsinki 1964 as revised in 2013 and the International Conference of Harmonization Guidelines for Good Clinical Practice (ICH GCP E6 guidelines). In accordance with French laws, the trial was authorized by the French national drug agency (Agence Nationale de la Sécurité du Médicament, ANSM) on 23 August 2017. The study was also approved by the Institutional Review Board (Comité de Protection des Personnes CCP Ile-de-France X) on 5 September 2017 (n°2017-A01684–49).

### Participants

All patients admitted to the participating centers are screened against eligibility criteria. Inclusion criteria are as follows: adult patients (aged 18 years or older); hospitalized in ICU for less than 24 h, and septic shock evolving for less than 12 h. Septic shock is defined according to the 2016 revised standard consensus criteria: documented or suspected infection, lactatemia > 2 mmol/l, and norepinephrine administration to maintain a mean arterial pressure (MAP) above 65 mmHg after adequate fluid resuscitation, [22]. Non-inclusion criteria are as follows: having expressed the wish not to be resuscitated, contraindication for the use of a brachial cuff on both arms, intercurrent disease with an expected life expectancy of less than 24 h, cardiac arrest, pregnant or breastfeeding women, previous inclusion in the study or participation in another interventional study*,* lack of French national health insurance coverage, and being under judicial protection.

### Informed consent

Informed consent that details the study design and outcomes must be obtained prior to inclusion. If the patient is able to consent but cannot write, an oral consent can be obtained in the presence of an impartial witness, independent of the study investigator. It is expected that, in most cases, it will not be possible to obtain prospective consent from the patient due to incapacity resulting from critical illness and its treatment. Under such conditions, written consent is sought from next of kin. All surviving patients are informed about the trial once they regain capacity and are asked to give consent to their ongoing involvement in the trial. Patient or their relatives can withdraw their consent and discontinue the participation in the study at any time upon request.

### Randomization

After consent, eligible patients are randomly assigned to received RECO or not. Randomization is stratified by center on a 1:1 basis in permuted blocks. Randomization is performed online using the ClinSight™ software (Ennov Clinical Software, Paris, France).

### Intervention

As soon as possible after randomization to either the RECO group or the Control group, a standard CE-approved blood pressure cuff (Tensiomètre Manopoire Duo Colson®, Drive DeVilbiss Healthcare, Frouard, France) is placed, deflated, around one of the patient’s upper arms. In line with the recommendations for non-invasive measurement of blood pressure, the size of the cuff is chosen to accommodate the patient’s arm [23]. In the RECO group, ischemic conditioning consists of four cycles of cuff inflation to 200 mmHg for 5 min and then deflation to 0 mmHg for another 5 min (40 min total duration of the intervention). Both the safety and the efficacy of this standard protocol has been demonstrated in previous clinical trials [5–7, 9–13]. In the Control group, the cuff is left in place, deflated, for 40 min (sham procedure). The RECO or the sham procedure is repeated at 12 and 24 h after inclusion. Standard operation procedures (SOP) describing the interventions are available for all investigators. A written checklist is completed by the investigator performing the intervention to ensure protocol adherence. With the exception of the tested intervention, patients receive standard care in accordance with international guidelines [2].

### Primary outcome

The primary outcome of this trial is the severity of sepsis-induced MOF as assessed by the mean daily SOFA score from inclusion (day 0) to the fourth day after inclusion (day 4) or to the day of death if it occurs before day 4. The SOFA score is an objective tool to quantitatively describe the degree of organ dysfunction over time [18–21]. The mean daily SOFA score, which closely correlates with mortality in critically ill patients [19], is regularly used as a surrogate outcome for death in sepsis trials [24, 25]. The choice of a mean SOFA score helps to solve the “truncated by death” issue as all patients contribute scores and no imputation of data is needed if a patient dies. As shown in Table 1, the SOFA score ranges from 0 to 24 (higher scores indicate more severe organ failure), with 0 to 4 points assigned for each of six organ dysfunctions (i.e., respiratory, coagulation, liver, cardiovascular, central nervous system, and renal). As previously described, a daily SOFA score is calculated using the most abnormal clinical and/or biological values in the previous 24 h (or from the start of the considered 24-h period to death) [18–21]. Predefined rules for dealing with potential missing data have been established.

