### Data collection

The following data are recorded: demographics, concurrent medical conditions and comorbidities, sepsis diagnosis and treatment, severity of illness and organ dysfunction scores, vital signs and laboratory results, characteristics of the RECO procedure, life-sustaining therapies, and outcomes (follow-up: 90 days). Data are entered into a web-based electronic case report form (eCRF, ClinSight™ software) from patient notes (source) under the supervision of the trial site investigators. A unique numeric identifier is assigned to each patient. All the data entered in the study database are anonymized in order to ensure confidentiality. Assessments are made at inclusion, and on days 1, 2, 3, 4, 28, and 90. From the eCRFs, the trial database will be established. According to French laws, all original records (including informed consent forms, eCRF, and relevant correspondences) will be archived at trial sites for 25 years.

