### Sample size

No a priori evidence suggests the magnitude of the effect of RECO on the severity of MOF in septic shock patients. Under the alternative hypothesis of an expected difference of half the standard deviation (effect size: 0.5) of the mean daily SOFA score of the first 4 days after inclusion, at least 168 patients have to be enrolled to reject the null hypothesis of a similar mean SOFA score in both arms with a power of 90% (β = 10%) and type 1 error at α = 5% (two-tailed). Even though there is no published data regarding the mean daily SOFA score in patients meeting our eligibility criteria, one can assume a mean value ranging from 8 to 12 with a standard deviation ranging from 4 to 6. Thus, for example, if the standard deviation is found to be 4, then a decrease of 2 or more in the mean daily SOFA score will be needed to reach significance. We planned to recruit an additional 7% patients (*n* = 12) to account for potential loss to follow-up and withdrawal of consent. Thus, the planned sample size is 180 patients (90 patients in each arm). Based on the enrollment capacity of the participating centers, the recruitment is expected to be completed within 18 months. The sample size was calculated with the use of nQuery Advisor, version 5.0 (Statistical solution, Cork, Ireland).

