### Statistical analysis

The trial will end once 180 patients have been enrolled and have completed the 90 days’ follow-up. No interim analysis will be planned for this study. A full statistical analysis plan will be drawn up by the CIC (Lyon) before the trial database is locked. Prior to performing any statistical tests or fitting statistical models, an exploratory analysis of the baseline variables will be completed. The number and pattern of missing data for baseline variables and outcomes will be established by forming appropriate tables and likely causes of any missing values will be investigated. Variables will be expressed as median and interquartile range (IQR) or number and proportion, as appropriate. Statistical analyses of the primary and secondary efficacy endpoints will primarily be based on the intent-to-treat population. The main analysis of the primary endpoint, the mean daily SOFA score from day 0 to day 4, will be performed by fitting a mixed-effects linear model with a fixed effect for the assigned treatment and a random centre effect. Secondary outcomes will be analyzed with appropriate statistical methods including the Wilcoxon rank sum, chi^2^ and log-rank tests. The same analysis will be performed on the per-protocol population, which will include all randomized patients who have received the intervention in accordance with the allocated group without any major protocol deviation. A probability value of < 0.05 will be considered to indicate statistical significance and 95% confidence intervals will be calculated.

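### The primary endpoint averages five SOFA scores including day 0, while the power is set on the first four days after inclusion; if day 0 is pre-treatment, the 90% power depends on which mean carries the 0.5 SD.

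*Protocol article*

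**What the plan says.** Five statements in the protocol article bear on this point.

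- **Endpoint.** Primary outcome defines it as "the mean daily SOFA score from inclusion (day 0) to the fourth day after inclusion (day 4"), or to the day of death if earlier. Statistical analysis repeats the window: "the mean daily SOFA score from day 0 to day 4". With no death before day 4, that is five scores.
- **How a daily score is built.** According to Primary outcome, "a daily SOFA score is calculated using the most abnormal clinical and/or biological values in the previous 24 h", with a shortened period for the day of death.
- **When scores are taken.** Data collection: "Assessments are made at inclusion, and on days 1, 2, 3, 4, 28, and 90".
- **When treatment starts.** Intervention has the cuff placed "As soon as possible after randomization to either the RECO group or the Control group".
- **What the power refers to.** Sample size assumes "an expected difference of half the standard deviation (effect size: 0.5") "of the mean daily SOFA score of the first 4 days after inclusion". This gives 168 evaluable patients for 90% power at two-sided 5%, raised to 180. The section also says that "No a priori evidence suggests the magnitude of the effect of RECO on the severity of MOF in septic shock patients", and illustrates the effect as 2 points at an SD of 4.

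The main model named in Statistical analysis has a fixed treatment effect and a random centre effect. No baseline SOFA term is mentioned.

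**The concern.** The endpoint window and the power window are worded differently: five scores counted from inclusion against the first four days after it. This matters because the extra score is probably a baseline value. A score taken at inclusion that looks back 24 h contains no treated time, and the first procedure comes only after randomisation. Such a score has the same expectation in both arms, so it pulls the difference in means towards zero. It also brings baseline severity into the outcome, and the named model does not remove it.

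The stakes are sensitivity and interpretation. A real effect of the planned size on the days that treatment can influence might be detected less often than stated. The reported difference in points would also understate what happens on those days. That second consequence counts here, because the Discussion presents the trial as a source of design data for later trials with a hard endpoint.

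**Working it through.** **1. The plan's own figure.** Inputs from Sample size: effect 0.5 SD, power 90%, two-sided 5%.

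n per arm = 2 × (1.960 + 1.282)² / 0.5² = 84.06

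This agrees with 84 × 2 = 168 (170 if rounded up per arm, 172 by the t-test). Power at 0.5 SD by the normal formula is 90.0% with 84 per arm and 91.8% with the planned 90. The stated arithmetic is sound for whichever mean carries the 0.5 SD.

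**2. Effect of a day-0 score that treatment cannot change.** Let D be the day-0 score and M the mean of days 1–4. For a patient with all five scores:

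Y = 0.2 D + 0.8 M

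The raw effect on Y is 0.8 times the effect on M. At SD 4, 2.0 points on M becomes 1.6 points on Y. For a patient scored only on days 0 and 1, day 0 has weight 1/2, so the dilution is larger after early death.

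**3. Standardised effect if the 0.5 SD is on days 1–4.** Set SD(M) = 1, SD(D) = s and corr(D, M) = r.

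Var(Y) = 0.04 s² + 0.64 + 0.32 r s; standardised effect = 0.4 / √Var(Y)

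The protocol gives neither s nor r. I assume s = 0.75–1.0 and r = 0.4–0.8. Power is by the two-sample t-test, two-sided 5%; centre effects and early deaths are left out.

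| s | r | SD(Y) | Effect | Power, 84/arm | Power, 90/arm |
|---|---|---|---|---|---|
| 0.75 | 0.4 | 0.871 | 0.459 | 84.1% | 86.5% |
| 0.75 | 0.8 | 0.924 | 0.433 | 79.6% | 82.3% |
| 1.0 | 0.4 | 0.899 | 0.445 | 81.8% | 84.4% |
| 1.0 | 0.6 | 0.934 | 0.428 | 78.8% | 81.5% |
| 1.0 | 0.8 | 0.967 | 0.413 | 75.9% | 78.8% |

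The standardised effect falls from 0.50 to 0.41–0.46, a loss of 8–17%. This is less than a fifth because SD(Y) is below 1 throughout. In the limit s = 1, r = 1 the SD does not change: the effect is 0.40 and power is 73.1% (84 per arm) or 76.1% (90 per arm).

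**4. If the 0.5 SD is on the day 0–4 mean.** Power is as in step 1. At SD 4 the effect is 0.5 × 4 = 2 points on Y. With none on day 0, this requires 2 / 0.8 = 2.5 points on days 1–4.

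**5. What a day-0 covariate does.** Given D, the only part of Y still varying is 0.8 M. In patients with all five scores, the adjusted test of Y is therefore the same as the adjusted test of M. The residual SD of M is √(1 − r²), so a 0.5 SD effect on M becomes 0.5 / √(1 − r²): 0.546 at r = 0.4 and 0.625 at r = 0.6. Power with 84 per arm is then about 94% and 98%, and above 99% at r = 0.8. The covariate recovers the lost power, but the difference in Y is still 0.8 of the difference in M, in points.

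**The case against.** **The 0.5 SD is nominal.** It has no prior evidence behind it, and the phrase about the first four days may be loose wording for the endpoint itself. The 90% is then correct. This stands: a reader might infer that the trial is underpowered, but the protocol does not establish that. It establishes only that the power refers to a mean that is not clearly the one analysed.

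**The timing of day 0 is inferred.** No sentence calls it pre-randomisation. Primary outcome also speaks of the start of a 24-h period when it describes deaths, patients may have been in the ICU for less than 24 h, and the schedule figure is not available here. If day 0 means the 24 h starting at inclusion, it is largely treated time and the dilution shrinks or disappears. This also stands. But the look-back wording would then need correcting, and five 24-h periods would still not match four days.

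**The comparison remains valid.** A baseline component is balanced in expectation by randomisation. It causes no bias between arms under the null and no inflation of type I error. The reading that it does finds no support. Daily scores and their change from day 0 to day 4 are already secondary outcomes, so later behaviour will be visible.

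**Baseline adjustment may be in the SAP.** Agreed; its absence from the article is not counted as a fault. It appears below only as the remedy.

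**Replacing the primary endpoint is costly.** The trial is open-label and was already recruiting. Days 1–4 alone could also leave a patient who dies on day 0 without a score if day 0 turns out to be treated time. For these reasons I do not recommend replacing it.

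**Conclusion.** The point holds in conditional form. The endpoint window and the power window do not match in wording. On the most natural reading, one of the five averaged scores cannot respond to treatment. The raw difference is then diluted by exactly a fifth in patients with all five scores, and by more after early death.

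What this does to power depends on what the 0.5 SD refers to:

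- On days 1–4: power is about 76–84% with 84 per arm and 79–87% with 90, against the stated 90%. This rests on the assumed day-0 SD (0.75–1.0 times that of the day 1–4 mean) and correlation (0.4–0.8).
- On the day 0–4 mean: 90% stands, at the price of about 2.5 points on days 1–4 at SD 4.

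A reader might infer that the standardised effect falls by 20%, or that the trial misses its power as a matter of fact. Neither follows: the standardised loss is 8–17% on these assumptions, and any shortfall depends on two unstated definitions. This is a needed clarification with a cheap gain in precision, not a flaw that invalidates the trial.

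**What to change.** 1. In Primary outcome, state when the day-0 SOFA is measured relative to randomisation and the first procedure, and which 24 h it covers.
2. In Sample size, name the mean that carries the 0.5 SD and restate the figure to match. Either give the power for a 0.5 SD effect on days 1–4 with the assumed SD and correlation, or keep 90% and give the detectable difference on both the day 0–4 mean and days 1–4 (2 and 2.5 points at SD 4).
3. If day 0 is confirmed as pre-treatment, add day-0 SOFA as a fixed covariate in the primary mixed model, and report the baseline-adjusted day 1–4 mean as a key supportive analysis. Keep the registered day 0–4 endpoint. Fix this in the SAP before database lock.
4. If day 0 instead covers time after inclusion, correct the look-back wording and align the four-day phrase with the five scores. Do not use day 0 as a covariate in that case, because it would be affected by treatment.

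The cost is a clarified definition, one restated power sentence and a little more analysis. The scores at inclusion and on days 1–4 are already collected, so no new data and no more patients are needed.
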